### Study outcomes

Table 
1 indicates the **adherence**, **graft**, and **adverse** outcomes being measured in all participants. The planned primary outcome is daily "*taking adherence*", defined as the proportion of daily prescribed doses taken, as measured using electronic monitoring (EM). Because no one method of measuring adherence is considered a gold standard, we will measure adherence in several ways including pharmacy dispensing records, self-report using the MAM-MM, and variability in tacrolimus or sirolimus trough levels
[36-38]. We will also consider a composite of variability in tacrolimus or sirolimus trough levels and self-report such as the ‘system for integrated adherence monitoring’
[39].

**Table 1 T1:** Outcome measures

**Category**	**Measures**	**Frequency**
**Adherence outcomes**	**Electronic monitoring**	Continuously monitored
	● Taking adherence (% prescribed doses taken each day)	
	● Timing adherence (% doses taken within 2 hours of scheduled time each day)	
	● Drug holidays (missing ≥2 consecutive doses)	
	**Pharmacy refills**	All refills during study interval
	● Taking adherence (% prescribed doses taken over entire intervention period)	
	**Variability in tacrolimus or sirolimus trough levels**	Monthly levels as measured for clinical care
	● Standard deviation calculated over 6-month intervals	
	**Self-report** (Medical Adherence Measure- Medication Module)	3-month intervals
	● Taking adherence (% prescribed doses taken, in 3-month intervals)	
	● Timing adherence (% doses taken within 2 hours of scheduled time, in 3-month intervals)	
	● Drug holidays (missing ≥2 consecutive doses)	
**Graft outcomes**	**Graft failures or deaths** (# failures/person-year of follow-up)	All failures during study interval
	● Failure defined as loss of graft function requiring return to dialysis or death from any cause	
	**Acute rejections** (# rejections/person-year of follow-up)	All rejections during study interval
	● Biopsy-proven and presumed rejections, defined as rejections diagnosed by the treating physician based on >20% rise in creatinine	

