### Statistical analysis plan

The primary analysis will use intention-to-treat principles; as-treated secondary analyses will also be done. Daily taking adherence will be determined for each participant for each day of follow-up
[45]; the median daily taking adherence will be determined for participants in each of the intervention and control groups, and plotted against time. This will allow assessment of changes in adherence over the intervention interval for each group. We will calculate the area under the curve (AUC) for the entire intervention interval for each group, and compare AUCs using a two-sided, independent two samples t-test or Wilcoxon test. Greater AUC will reflect greater adherence. To account for possible imbalances between groups, and to test for differences in the patterns of change in taking adherence over time between the intervention and control groups, we will use linear mixed-effects models, adjusting for potential confounders. We will use the same approach to analyze the secondary adherence outcomes.

Percent change in estimated glomerular filration rate (eGFR) over the intervention interval will be compared between groups using a 2-sided, independent two samples t-test or a Wilcoxon rank sum test, as appropriate to the distribution of the data. Acute rejections and graft failures will each be expressed as a rate per person-month of observation, and compared between intervention and control groups using Poisson regression.

The multivariable linear mixed-effects models developed for the primary aim will be extended to include center and system characteristics and accessibility factors that are fixed over time (i.e. Canada vs. US), as well as time-varying center, system, and accessibility variables (i.e. insurance status, perceived accessibility). Similar analyses will be undertaken considering secondary adherence outcomes. We will use these models to identify center, system, and accessibility characteristics that are independently associated with adherence.

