### Power considerations

Our preliminary electronic monitoring studies in adolescent transplant recipients found a mean (±standard deviation (SD)) taking adherence of 79% ± 33 at one site and 78% ± 29 at another site (unpublished). With 75 participants per group, setting alpha at 0.05, we will have 85% power to detect a 20% difference in taking adherence, using a two group t-test, assuming a common SD of 32 (40% of the mean). Preliminary studies suggested substantially lower variability in adherence after intervention compared with before. If the SD is 25% in the intervention group, and 40% in the control group, we will have 95% power to detect a 20% difference in taking adherence, or 80% power to detect a 16% difference. Based on preliminary studies indicating a 26% improvement in adherence after intervention with dose reminders, and on published work
[12], it is reasonable to expect a 20% improvement in adherence when a single level intervention is applied. Effect sizes may be larger with a multi-level intervention.

Due to low event rates and large variability in graft function, statistical power is extremely limited to detect differences between intervention and control groups for graft outcomes; these analyses are considered exploratory.

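### The primary comparison is worded as one AUC of daily group medians per arm, which the named tests cannot use, and that median would probably hide the effect the trial is powered for

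*Protocol article*

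**What the plan says.** The Statistical analysis plan section of the protocol article sets out the primary analysis in four steps.

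1. "Daily taking adherence will be determined for each participant for each day of follow-up".
2. "the median daily taking adherence will be determined for participants in each of the intervention and control groups, and plotted against time".
3. "We will calculate the area under the curve (AUC) for the entire intervention interval for each group".
4. The plan will "compare AUCs using a two-sided, independent two samples t-test or Wilcoxon test".

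The only curve described before the AUC step is the group-median curve, and no AUC per participant is mentioned. The section then adds a further analysis to deal with imbalances and to test for differing patterns over time: "we will use linear mixed-effects models, adjusting for potential confounders". The secondary adherence outcomes are to be handled in the same way.

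The Power considerations section reports preliminary studies that "found a mean (±standard deviation (SD)) taking adherence of 79% ± 33 at one site and 78% ± 29 at another site". It bases the sample size on a two-group t-test with 75 participants per group and a common SD of 32, and gives 85% power for a 20% difference.

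**The concern.** There are two problems, and the first needs no assumption.

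**Unit of analysis.** If the AUC is taken under each group's median curve, each arm contributes one number. A t-test has no within-arm variance to work with, and a Wilcoxon test has one observation per side. The power statement concerns a different quantity, the spread of adherence between participants.

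**Choice of summary.** Daily adherence is the share of a day's few doses, so it takes only a few values and piles up at 100%. The median of such data can stay at the ceiling while the mean moves a good deal. A curve of daily medians could then look the same in both arms even if the intervention works as hoped.

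This is the primary comparison of the trial. Whoever runs the analysis would have to choose the unit, and possibly the summary, after the data are in.

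**Working it through.** **1. The plan's own power figure.** Inputs from Power considerations: n = 75 per group, two-sided alpha 0.05, SD 32 (40% of the mean), difference 20%. Read as relative, 20% of 79 is 15.8 points.

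- Standard error = 32 × √(2/75) = 5.23 points.
- Power = Φ(15.8/5.23 − 1.96) = Φ(1.06) = 0.856 (0.852 with the noncentral t). Using the ratio 0.20/0.40 instead gives 0.865 (0.860).
- A difference of 20 absolute points gives 0.969, which does not match.

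The stated 85% is therefore the power of a comparison of 75 participant values with 75, for a difference of about 16 points.

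**2. The analysis as worded.** One AUC per group is 1 value against 1 value. The two-sample t-test has 1 + 1 − 2 = 0 degrees of freedom. The Wilcoxon test has two possible rankings, so it cannot reach p < 0.05.

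**3. Where the daily median sits.** The document does not give the number of doses per day, k, so k is an assumption and a range is shown. The group median is 100% when more than half the participants are at 100% that day. Let P be that share and m the mean. Anyone below 100% is at most at (k − 1)/k, so

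m ≤ P + (1 − P)(k − 1)/k, which gives P ≥ 1 − k(1 − m).

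For k = 2 and m = 0.79, P ≥ 1 − 2 × 0.21 = 0.58. Two further columns use the SD: as the SD of daily values (smallest P compatible with mean and SD, by linear programming), and as the SD between participants (beta-binomial model). For the latter with m = 0.78, SD 0.29 and k = 2: f = 0.78 × 0.22/0.29² − 1 = 1.040, a = 0.78f = 0.811, a + b = f, and P = 0.78 × (a + 1)/(f + 1) = 0.692.

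Each cell gives the 79% (SD 33) site, then the 78% (SD 29) site.

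| k | Smallest P, mean alone | Smallest P, mean and SD of daily values | P, SD between participants |
|---|---|---|---|
| 1 | 0.79 / 0.78 | not applicable (the mean fixes the SD) | 0.79 / 0.78 |
| 2 | 0.58 / 0.56 | 0.676 / 0.605 | 0.733 / 0.692 |
| 3 | 0.37 / 0.34 | 0.619 / 0.518 | 0.701 / 0.640 |
| 4 | 0.16 / 0.12 | 0.562 / 0.430 | 0.679 / 0.604 |
| 6 | 0 / 0 | 0.448 / 0.255 | 0.650 / 0.555 |

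The intervention arm, if the 20% relative improvement occurs, has a mean of 78 × 1.2 = 93.6%. The mean alone then gives P ≥ 1 − 4 × 0.064 = 0.744 at k = 4, so its median is 100%. Only the control arm is in doubt.

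**4. What the two curves would show.** Simulation with 75 per arm, 365 days, 300 runs per k. Control: mean 78%, SD 29 between participants. Intervention: mean 93.6%, assumed SD 20. Participant adherence is beta-distributed, with independent doses and no missing days.

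| k | Days with control median at 100% | Mean height of control curve | Gap from intervention curve (100%) |
|---|---|---|---|
| 1 | 100% | 100% | 0 |
| 2 | 99.98% | 99.99% | 0.01 points |
| 3 | 99.3% | 99.75% | 0.25 points |
| 4 | 96.4% | 99.1% | 0.9 points |

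The true difference is 15.6 points.

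**5. One value per participant.** Under the plan's own inputs the power is 85–86% (step 1). In a simulation with k = 2, control mean 79% (SD 32) and intervention mean 94.8% (assumed SD 20), a t-test on participant means had 96% power. It exceeds 85% because the assumed intervention SD is smaller. On a scale bounded at 100%, a mean of 94.8% cannot have an SD above √(0.948 × 0.052) = 22%.

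**The case against.** The best defence is that participant-level AUCs were meant. Daily adherence is determined for each participant, the median curve is introduced to show change over time, the named tests need one value per participant, and the power calculation uses the participant as the unit. That is probably the intention, and it makes this a matter of rewording rather than redesign. It does not rescue the text: the AUC is stated to be for each group, and the only curve before it is the group median.

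The defence is also right that the ceiling depends on a number the document does not give. Table 2 shows 117 of 125 participants (48 + 69) on two or three immunosuppressive drugs, so k could exceed four if each drug counts as a dose. The Adherence monitoring section records compartment openings, which suggests counting dosing times, but no counting rule is stated.

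Three stronger readings are tempting and are not supported:

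- *A false-positive rate far above 5% because days would be used as the sample.* The plan nowhere proposes this. Where the medians sit at 100% there would be no variation to test: with no true difference and k = 2, 96% of simulated runs had none.
- *The linear mixed model is invalid for bounded daily data.* The article does not state the outcome scale or the error structure. Those belong in a full analysis plan, and another model class would be a preference.
- *The trial cannot show its effect at all.* The mixed models can use participant data. The problem lies in the stated AUC comparison.

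**Conclusion.** The concern holds in two parts.

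- **Unit: firm.** The AUC comparison as worded cannot be carried out, and it does not match the participant-level t-test that gives the stated power. This rests on the text alone.
- **Median: conditional.** At a mean of 78–79% the daily median is 100% with one or two doses a day. With three, this follows only if the reported SD is also used, and with four it is likely but not guaranteed (the smallest P at the second site is 0.43). Both statements assume that the unpublished preliminary means from two sites hold in the control arm for 12 months, and the simulated gaps also rest on the assumed intervention SD. On those terms a true difference of about 16 points shrinks to less than 1 point on the planned curves.

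A reader might infer that both curves must sit at exactly 100%. The documents do not support that without the number of doses per day.

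**What to change.** Reword the primary analysis as follows.

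- State that the participant is the unit of analysis.
- Compute one value per participant over the intervention interval: either doses taken divided by doses prescribed, or the participant's mean daily adherence (own AUC divided by days observed). Name one, because the two differ if the number of prescribed daily doses changes. The first matches the outcome definition in the Abstract.
- Compare arms on that value with one pre-named two-sample test in place of the open choice between two, and report the mean difference with its 95% CI. The power section already rests on the t-test.
- Keep the daily group curve as description only, preferably as the daily mean or the share of participants at 100%.
- Carry the same wording to the secondary adherence outcomes wherever they inherit this approach. The linear mixed models can stay.

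The cost is wording in the protocol and analysis plan. It needs no new data, no extra participants and no change to the sample size calculation. It should be settled before outcomes are compared by arm, so that the unit and the test are not chosen after the results are known.

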**Design and methods:**

TAKE-IT is a multicentre, prospective, open-label, parallel arm randomized controlled trial that aims to determine the effectiveness of a clinic-based intervention, including *educational, organizational,* and *behavioural* components, in improving immunosuppressive medication adherence among adolescent and young adult kidney transplant recipients. Individuals between 11 and 24 years of age who are at least 3 months post-transplant and followed in one of the eight participating pediatric kidney transplant programs, or their affiliated adult transplant programs are eligible to participate. All participating centers are tertiary care pediatric hospitals in Canada or the United States. Adherence is monitored using an electronic multi-dose pillbox for all participants during a 3-month run-in period, followed by a 12-month intervention interval. The primary outcome is ‘taking adherence’, defined as the proportion of prescribed doses of immunosuppressive medications that were taken, as measured using electronic monitoring.

All participants meet with the study ‘Coach’ at 3 month intervals. The intervention, administered by trained lay personnel, targets common adherence barriers. In addition to forming an Adherence Support Team, intervention participants identify personal barriers to adherence and use Action-focused problem-solving to address them, have their electronic adherence data fed back to them, and have the option to receive email, text message, or visual cue dose reminders. Participants in the control group meet with the coach but do not receive the other components of the intervention. The study aims to have 75 participants in each group complete the study.

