### Randomization and blinding

Participants are randomized at enrolment in age strata (11–13 y., 14–16 y., 17–19 y., 20–24), by site, in blocks of 4. Allocation to intervention or control group is concealed from participants, clinical care providers, and study personnel at enrolment and during the first two months of the run-in period. Group allocation is revealed to study personnel one month prior to the 3-month visit. Blinding is not feasible to maintain with the proposed multi-component intervention.

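### The primary AUC comparison is unadjusted, so it leaves unused each participant's run-in adherence and the age and site randomisation strata; the cost is precision, not validity.

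*Protocol article*

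**What the plan says.** All statements are in the protocol article.

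- **Primary comparison** (Statistical analysis plan). The plan is to "compare AUCs using a two-sided, independent two samples t-test or Wilcoxon test", with AUC taken over the intervention interval. No covariate is mentioned. A two-sample test needs one value per participant, so I read this as a comparison of participant-level AUCs.
- **Adjusted models** (same section). Linear mixed-effects models are planned for two purposes. One begins "To account for possible imbalances between groups"; the other is to test whether the pattern over time differs by group. They adjust for possible confounders that are not listed. The section later describes these models as developed for the primary aim, and extends them with centre, system and accessibility variables for a secondary aim.
- **Power** (Power considerations). "With 75 participants per group, setting alpha at 0.05, we will have 85% power to detect a 20% difference in taking adherence", using a two-group t-test and a common SD of 32.
- **Run-in** (Abstract, Design and methods). Every participant is monitored electronically "during a 3-month run-in period, followed by a 12-month intervention interval". Baseline assessment confirms that no intervention is applied in the run-in.
- **Strata** (Randomization and blinding). "Participants are randomized at enrolment in age strata", in four bands, and by site, in blocks of 4. There are eight centres.

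**The concern.** Earlier adherence, measured in the same person on the same device, is likely to be among the best predictors of later adherence. The trial collects it from everyone before treatment starts, and the primary test does not use it. Nor does that test use the age and site strata, although the randomisation was built on them.

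Two things are at stake. First, the primary confidence interval is wider than it needs to be. Second, the headline estimate is exposed to chance differences between arms in run-in adherence. An adjusted estimate from the mixed models would then stand beside an unadjusted primary one, and the article does not say which takes precedence if they differ.

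**Working it through.** **Inputs from Power considerations:** 75 completers per arm, alpha 0.05, SD 32, and pilot results of "taking adherence of 79% ± 33 at one site and 78% ± 29 at another site". The two-sided test comes from the Statistical analysis plan. The correlation r between run-in and intervention-interval adherence is not given. I assume 0.3 to 0.7.

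**Step 1: reproduce the stated 85%.**
SE of the difference = 32 × √(2/75) = 5.226.
Power ≈ Φ(difference/SE − 1.96).
- Reading 20% as relative to a mean of 79%: difference = 0.20 × 79 = 15.8 points; 15.8/5.226 = 3.02; power 85.6% (85.2% with the noncentral t).
- Reading 20% as percentage points: 20/5.226 = 3.83; power 96.9%.

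Only the relative reading returns the stated figure, so 15.8 points is used below.

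**Step 2: add run-in adherence as a covariate.**
Residual SD = 32 × √(1 − r²). Equivalent unadjusted sample = 150/(1 − r²). The detectable difference at 85% power is (1.960 + 1.036) × residual SD × √(2/75).

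| r (assumed) | Variance removed (r²) | Residual SD | Equivalent completers | Power at 15.8 points, normal / noncentral t | Detectable difference, 85% power |
|---|---|---|---|---|---|
| none | 0% | 32.0 | 150 | 85.6% / 85.2% | 15.7 |
| 0.3 | 9% | 30.5 | 165 | 88.7% / 88.3% | 14.9 |
| 0.5 | 25% | 27.7 | 200 | 93.7% / 93.4% | 13.6 |
| 0.7 | 49% | 22.9 | 294 | 98.9% / 98.8% | 11.2 |

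**Step 3: the strata.**
If age and site explain a share f of the variance, stratified randomisation makes the true SE smaller than the unadjusted test assumes, by a factor of √(1 − f). The actual two-sided error rate is then 2 × [1 − Φ(1.96/√(1 − f))]. The share f is also an assumption.
- f = 5%: actual alpha 0.044; power 86.2% unadjusted against 87.3% with the strata in the model.
- f = 20%: actual alpha 0.028; power 88.3% against 92.2%.

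The strata therefore matter less than run-in adherence, and the unadjusted test errs on the conservative side.

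**Step 4: cost in degrees of freedom.**
Run-in adherence 1, age 4 − 1 = 3, site 8 − 1 = 7, total 11. Error degrees of freedom fall from 148 to 137. At the same residual SD this changes power by less than 0.1 percentage point. The full age-by-site cross would have 8 × 4 = 32 cells with about 150/32 ≈ 5 completers each, so main effects are the sensible form.

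**The case against.** The strongest reply is that the plan is coherent as it stands. The test is valid, the sample size was computed for that same test with the full SD, and the stated power reproduces. The mixed models belong to the primary aim and deal expressly with imbalance. A journal article may leave their covariate list to a SAP that is not shown here.

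Most of this is right, and it limits the point in four ways.

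- **No bias.** A reader might infer that the unadjusted result would be wrong. It would not: randomisation protects it, and ignoring prognostic strata only makes it conservative.
- **The mixed models are not demoted.** A reader might take them as merely secondary. The article ties them to the primary aim. What can be said is that they are not the test named for the AUC comparison or used for power, and that their stated purposes are imbalance and time pattern, not precision.
- **Run-in adherence is not excluded.** A reader might conclude that it is used nowhere. It is not named, but the unlisted confounders could include it, and an unlisted set is not in itself a defect of a condensed article.
- **No post hoc selection is stated.** The article does not say when or how confounders are chosen, so a charge that they are picked after seeing imbalance has no support in the text.

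The size of the gain is also uncertain. At r = 0.3 power rises by only about 3 percentage points. A linear model with many terms also gives up the Wilcoxon option's robustness for a bounded, possibly skewed outcome, unless the remedy allows for that.

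The objection does not remove the core. The article states a specific primary test, and a more precise one is available from data already being collected.

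**Conclusion.** The point holds as one of efficiency. The stated primary comparison uses neither run-in adherence nor the randomisation strata, and the adjusted models do not name run-in adherence or the age strata. With r between 0.3 and 0.7, adjustment for run-in adherence alone would remove 9% to 49% of the residual variance, and the difference detectable with 85% power would fall from 15.7 points to between 14.9 and 11.2. Accounting for the strata would add a smaller gain if they are prognostic.

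These sizes rest on the assumed r, on SD 32, and on the relative reading of the 20% difference. The direction does not depend on the exact r: any appreciable correlation outweighs the few degrees of freedom spent. The change is worth making, but the trial does not depend on it, since planned power is reached without it under the sponsor's own assumptions.

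**What to change.** Before outcome data are compared by arm, name one primary analysis: a model of each participant's mean daily taking adherence over the intervention interval (AUC divided by days) on arm, run-in taking adherence, age stratum and site, the last two as main effects. Use robust standard errors, or a rank-based ANCOVA if the outcome is skewed, with the rule for choosing written down in advance.

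Compute run-in adherence from days before allocation is revealed to study personnel, which is one month before the 3-month visit. This keeps the covariate free of any influence from knowledge of the arm.

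Keep the unadjusted t-test or Wilcoxon test as a sensitivity analysis. State that the mixed models support the primary result and describe the time pattern, and list their covariates.

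The cost is about 11 degrees of freedom and SAP wording. It needs no further participants, visits or data.

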	**Percent change in estimated glomerular filtration rate (eGFR)***	
	● Calculated as:	
	(eGFR at start of intervention – eGFR at study exit) ÷ eGFR at start of intervention	
**Adverse outcomes**	Deaths	All deaths during study interval
	Opportunistic viral infections (CMV, EBV, biopsy-proven polyoma virus nephropathy)	All infections during study interval
	Hospitalizations (# hospitalizations/ person-year of follow-up)	All hospitalizations during study interval
	Other medical conditions requiring treatment (# conditions/ person-year of follow-up)	All conditions during study interval

*eGFR is calculated from height and IDMS-standardized serum creatinine using the updated Schwartz formula
[40,41].

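### The exploratory eGFR comparison is an unadjusted test on percent change, so it gives up some precision and lets a chance imbalance in starting eGFR into the estimate

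*Protocol article*

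**What the plan says.** In the protocol article, Table 1 (Study outcomes) defines percent change in eGFR as the decline divided by the starting value: "eGFR at start of intervention – eGFR at study exit) ÷ eGFR at start of intervention". The Statistical analysis plan says that this quantity "will be compared between groups using a 2-sided, independent two samples t-test or a Wilcoxon rank sum test, as appropriate to the distribution of the" …

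The covariate-adjusted linear mixed-effects models in the same section are introduced for taking adherence. They are then extended to other adherence measures only: "We will use the same approach to analyze the secondary adherence outcomes". The later extension to centre, system and access factors also concerns adherence. No sentence applies an adjusted model to eGFR.

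Under Randomization and blinding: "Participants are randomized at enrolment in age strata (11–13 y., 14–16 y., 17–19 y., 20–24), by site, in blocks of 4". Under Power considerations: "statistical power is extremely limited to detect differences between intervention and control groups for graft outcomes; these analyses are considered exploratory".

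**The concern.** Dividing by the starting value is not the same as adjusting for it. When start and exit eGFR are imperfectly correlated, participants who start low by chance tend to show a percent gain, and those who start high tend to show a percent loss. Percent change therefore still depends on starting eGFR. That dependence adds noise to the group comparison, and a chance difference in starting eGFR between arms passes into the estimate.

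Comparing graft outcomes is a named secondary aim, and eGFR is the only continuous graft measure in Table 1. Power considerations gives large variability in graft function as one reason for the limited power. Part of that variability could be removed with a value that must be collected anyway. The covariate is pre-treatment, because no intervention is applied during the run-in.

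**Working it through.** **Inputs from the article.** 75 participants per group (the completer target), two-sided test, 8 sites and 4 age strata. The article states no eGFR effect, standard deviation, correlation or power, so there is no eGFR figure to reproduce.

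**Assumptions.** Equal spread of log eGFR at start and exit; start-exit correlation ρ from 0.5 to 0.95; coefficient of variation (CV) 35% for the simulation and the imbalance example; two-sided alpha 0.05, which the article states for adherence.

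**Step 1: precision.** Let σ² be the variance of log eGFR. The variance of log change is 2σ²(1−ρ). The ANCOVA residual variance is σ²(1−ρ²). Their ratio, ANCOVA to change, is (1+ρ)/2. Percent change is a monotone function of log change, so a rank test gives the same result on either, and the ratio is a reasonable guide for the t-test.

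The change-score test needs 75 ÷ [(1+ρ)/2] per arm to match ANCOVA with 75. Where ANCOVA has 80% power (standardised effect 2.8016), the change-score test has power Φ(2.8016 × √[(1+ρ)/2] − 1.96).

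| ρ | Variance ratio | Variance loss | n per arm to match 75 | Power when ANCOVA has 80% |
|---|---|---|---|---|
| 0.5 | 0.75 | 25% | 100 | 68% |
| 0.7 | 0.85 | 15% | 88 | 73% |
| 0.8 | 0.90 | 10% | 83 | 76% |
| 0.9 | 0.95 | 5% | 79 | 78% |
| 0.95 | 0.975 | 2.5% | 77 | 79% |

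**Step 2: simulation on percent change itself.** 2,000 trials per scenario, 75 per arm, log-normal eGFR, effect set for about 80% ANCOVA power. Monte Carlo error is about √(0.8 × 0.2 ÷ 2000) = 0.9 points. The strata here have no prognostic value.

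| ρ | t-test | Wilcoxon | ANCOVA on starting eGFR | ANCOVA plus 10 stratum terms |
|---|---|---|---|---|
| 0.7 | 72.4% | 71.5% | 79.8% | 77.0% |
| 0.8 | 73.4% | 72.8% | 78.5% | 76.4% |
| 0.9 | 75.6% | 74.8% | 78.9% | 75.6% |
| 0.95 | 77.4% | 75.8% | 78.4% | 75.4% |

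From ρ = 0.8 to 0.95 the gain of ANCOVA over the t-test falls from 5.1 to 1.0 points. The 10 fixed terms (7 for site, 3 for age) cost 2.1 to 3.3 points when they predict nothing. If the strata explain 10% of the residual variance, ANCOVA with strata reaches 82.4%, 80.8%, 80.8% and 80.0%, against 73.4%, 75.4%, 78.0% and 78.8% for the t-test.

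**Step 3: lower power.** The article says power for graft outcomes is extremely limited, so 80% is a generous reference point. With the same variance ratio, if ANCOVA had 30% power the change-score test would have 27.5% at ρ = 0.8 and 28.8% at 0.9. If ANCOVA had 20%, the figures would be 18.5% and 19.2%. The gain is then about 1 to 2.5 points.

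**Step 4: chance imbalance.** Log change has slope ρ − 1 on log starting eGFR. With CV 35%, the log standard deviation is √ln(1 + 0.35²) = 0.340. One standard error of the difference in starting values is 0.340 × √(2/75) = 0.056. An imbalance of that size shifts the estimate by 0.3 × 0.056 = 0.017 at ρ = 0.7, or 0.2 × 0.056 = 0.011 at ρ = 0.8. The effects at which ANCOVA has 80% power are 0.111 and 0.093, so the shift is about 15% or 12% of them.

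**The case against.** The case for leaving the plan alone has four parts.

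- **Validity and role.** A two-sample test on percent change controls type I error under randomisation and is unbiased over repeated randomisations. The outcome is declared exploratory, with no stated power and no primary inference. This stands. A reader might infer that the test is invalid or biased; the article does not support that. The shift in Step 4 exists only conditional on an imbalance that happens to occur.
- **Size.** Every eGFR input is assumed. A reader might infer a gain of 13 to 15 power points. That needs a correlation of 0.5 and a design with 80% power for eGFR; the article supplies no such correlation and says power is extremely limited. This stands too.
- **Skewness.** The option of a Wilcoxon test already deals with much of a skewed ratio. With normally distributed eGFR at a correlation of 0.9, a separate simulation found Wilcoxon level with ANCOVA or up to 2 points ahead. This narrows the point but does not remove it, since the rank test still ignores starting eGFR.
- **Cost of adjustment.** It is not free. Non-prognostic stratum terms can cancel the gain at high correlation. A log-scale model also needs a positive exit eGFR, whereas a rank test can place graft failures and deaths as worst outcomes. Both stand and shape the fix.

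A reader might also infer from Table 2, where the arms differ in primary disease and time since transplant, that starting eGFR is imbalanced. Table 2 does not report eGFR, so this is unknown.

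**Conclusion.** The point holds as a minor efficiency matter. The article states the eGFR test outright, and nothing elsewhere in it brings starting eGFR or the strata into that comparison. The direction of the loss is clear unless percent change happens to be unrelated to starting eGFR and the strata are not prognostic. Its size cannot be derived from the article: it is modest at assumed correlations of 0.8 to 0.95, larger at 0.5 to 0.7, and smaller in power terms when overall power is low. The calculations assume 75 per arm, equal spread at both times and, for the simulation, log-normal eGFR. The primary adherence result is not affected.

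**What to change.** Make the main eGFR comparison an ANCOVA of exit eGFR (log scale if skewed) on treatment group and start-of-intervention eGFR. Include age stratum and site parsimoniously, for example site as a random intercept. Report the adjusted difference, or the ratio on the log scale, with its 95% confidence interval. State how participants with graft failure or death enter the analysis. Keep a rank-based comparison of percent change, with those participants given the worst ranks, as a sensitivity analysis, and keep Table 1's percent change as a descriptive summary by arm.

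The change takes a few sentences of analysis text and no new data. It uses a few degrees of freedom. If all strata are fixed terms and not prognostic, it can cost up to about 2 to 3 power points; the random intercept is meant to limit this but was not simulated. The headline becomes an adjusted estimate instead of a raw percent change.
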